## Abstract

**Background:**

Available evidence on effectiveness of non-pharmacological interventions for cognitive and affective symptoms in Mild Cognitive Impairment (MCI) and the early stages of dementia is encouraging but still limited. Multifocal high-definition brain stimulation could detain the potential of improving these symptoms by modulating the activity of a fronto-temporal network. Moreover, combined electrophysiological measures might contribute monitoring the underlying neurophysiological effects. In this study protocol an innovative and integrated intervention for patients with MCI and early-stage dementia will be proposed, also exploring the modulatory role of some specific variables such as education and cognitive reserve.

**Method:**

Sixty patients with MCI and early-stage dementia will be enrolled in a crossover double-blind randomized controlled trial utilizing an integrated intervention combining conventional cognitive treatment with multifocal brain stimulation and electrophysiological recordings. A battery of standardized neuropsychological tests will be employed at several time points to monitor changes, and inferential statistics will identify the changes specifically associated with the intervention. Regression analyses will be performed to ascertain the extent to which education and cognitive reserve scores may influence intervention outcomes. Analysis of electrophysiological data will contribute characterizing responders to treatment.

**Discussion:**

The project will contribute to a transformation in the landscape of non-pharmacological interventions for MCI and dementia, integrating diverse techniques and levels of analysis within a unified, comprehensive approach.

**Trial registration:**

This study is registered at ClinicalTrials.gov database under registry number NCT06668610 on October 30, 2024.

## Background

1

As life expectancy increases and the population ages, the global prevalence of dementia is expected to continue to rise. It has been recently estimated that the number of people with dementia worldwide will increase from around 57 million cases in 2019 to 152 million cases in 2050 (1). The surge in the number of people living with dementia highlights the need for effective prevention and treatment strategies (2, 3). Pharmacological interventions have shown potential benefits in reducing cognitive decline in early dementia (4), but their overall effectiveness remains limited and warrants future advances. For this reason, in recent years the benefits of non-pharmacological interventions, such as exercise training, computerized cognitive training and cognitive stimulation, are currently being explored in dementia and its preclinical conditions (5). Within this context, non-invasive brain stimulation (NIBS), encompassing repetitive transcranial magnetic stimulation (rTMS) and transcranial direct current stimulation (tDCS), represents a safe and straightforward approach to modulating brain excitability and plasticity, with the potential to enhance cognitive functioning in individuals with dementia and Mild Cognitive Impairment (MCI). In particular, tDCS has the advantage of being highly portable, relatively non expensive and easy to use, thus being suitable even for development of telerehabilitation systems controlled by clinicians remotely (6).

Several systematic reviews and meta-analyses, however, have not provided conclusive data about effectiveness of NIBS delivered alone or combined with cognitive treatment on dementia and MCI. Teselink et al. (7) have found NIBS to significantly improve global cognition and affective symptoms relative to sham stimulation in patients with Alzheimer’s Disease (AD) and MCI. Subgroup analyses showed that these effects were mainly restricted to TMS and to patients with AD, while limited evidence was available for tDCS and MCI. Similar results were obtained by Simko et al. (8) who argued that TMS over the dorsolateral prefrontal cortex seemed to be effective in enhancing cognition in AD, whereas no clear effect was observed for MCI. In both studies no support was offered for combined cognitive stimulation therapy with NIBS intervention. A lack of relevant effects of tDCS in MCI was also confirmed by Saleh et al. (9), who called for implementation of neurophysiological methods to assess the possible brain mechanisms associated with the treatment and to identify possible markers of effective response to stimulation thus reducing variability of stimulation effects (10). These conclusions contrast with a recent systematic review and metanalysis by Yang et al. (11), according to which TMS in AD showed the best outcomes in improving global cognition, but relevant effects can be exerted by tDCS in AD and MCI as well. Crucially, Yang et al. supported a beneficial effect of NIBS combined with cognitive therapy.

Inconsistencies among the research reports could be ascribed to several factors including use of different methods to assess cognitive functions; moreover, evidence about effectiveness of tDCS in MCI is limited by the small number of studies targeting this issue, whereas more data are available on use of TMS in AD.

The objective of the present paper is to describe a protocol for the treatment of the cognitive and affective symptoms in MCI and dementia with several specific novel features. First, the protocol adopts multifocal stimulation of relevant brain structures thought to be involved in the genesis of the symptoms. While all previous studies focused on specific areas in the frontal and temporal cortex in separate treatment conditions, in the present project multifocal tDCS over such structures is proposed to the aim of maximizing distribution of direct current over the left fronto-temporal network (12). This specific feature follows recent studies describing a fronto-parieto-temporal network involved in cognitive (dys)functions which has been shown to be effectively modulated by brain stimulation (13, 14). Multifocal stimulation of such a network could strengthen the achievable outcomes by activating a larger scale network involved in cognitive and affective processes as compared to previous studies. Second, to address the issue of heterogeneity of stimulation effects, the proposed protocol combines electrophysiological measures (EEG) with brain stimulation (9). As shown in previous studies on healthy and brain damaged individuals, electrophysiological and neuroimaging techniques may contribute clarifying the mechanisms and brain response associated with brain stimulation (10, 15–18), also accounting for possible individual differences in response to stimulation. Crucially such integration would allow identifying good and bad responders to stimulation so to target individuals which may benefit the most from a given intervention (10). Third, this study protocol will further explore the variability in response to brain stimulation raised by previous studies, considering the relationship between some demographical and psychological factors with clinical and electrophysiological outcomes. Previous studies have shown a buffering effect of age on global cognitive response following brain stimulation interventions, with larger effects in younger populations (7), and a relevant association of cognitive functioning with cognitive reserve (and its proxies), as higher cognitive performance and better emotional response were associated with higher levels of cognitive reserve (3, 19). These variables will be embedded in the study protocol to allow a comprehensive interpretation of either positive or null effects, and to plan future research on the topic.

To achieve these purposes the present study protocol will adopt a double-blinded sham-controlled crossover experimental design in patients with MCI and early stages of dementia, combining brain stimulation and electrophysiological recording. The primary outcomes will be global cognitive functioning, anterograde verbal episodic memory and executive functions as well as affective symptoms. Secondary outcomes will be the level of functional independence in daily living and electrophysiological measures. Based on the available literature we expected to observe an effect of brain stimulation on cognitive and affective functions (7, 11). Moreover, we expect the use of EEG recording being able to provide findings useful to distinguish good and bad responders to the treatment based on individual analysis (9, 10). Finally, we hypothesize that demographic factors can modulate the possible outcomes, thus contributing to identify the patients most suitable for such intervention (3, 7).

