### Procedure

2.3

The participants will be initially informed about the objectives of the study in an introductory meeting involving also their family members. Following this meeting, the participants will provide their informed consent. No compensation or different treatment within the clinical institution practices will be reserved to participants included in the study. Participants will then undergo a neuropsychological battery exploring cognitive functions, affective symptoms and independence in daily living (T1). The same battery of tests will be repeated at the end of the first (T2) and of the second (T3) rehabilitation cycles. The intervention will involve two rehabilitation periods involving multifocal brain stimulation (real vs. sham with a crossover design) combined with cognitive stimulation therapy. EEG recordings with eyes-opened will be performed at the beginning and the end of each period of stimulation. The CONSORT Flow Diagram that will be ensued detailing enrolment, allocation, follow-up, and analyses is provided as Supplementary File.

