### Intervention

2.4

The intervention will consist of multifocal brain stimulation combined with cognitive training. In a cross-over design, 16 stimulation sessions (two sessions for week; freely scheduled from Monday to Friday on participants’ and institutional needs) will be delivered in two blocks (8 real and 8 sham stimulation sessions) for 10 weeks. The first and the last stimulation sessions of each block (namely sessions 1, 8, 9 and 16; Figure 1) will be preceded and followed by 5-min resting state EEG recordings with eyes-opened. Recruited participants will be randomly assigned to a “SHAM-REAL” stimulation group (G1) or a “REAL-SHAM” stimulation group (G2; Figure 1) by computer-generated random numbers; one investigator (FP) will manage generation of allocation sequence and participants’ assignment to the groups. The experimenters responsible for delivering the stimulation (LC) will be blind to the stimulation being delivered during each session. Throughout the study, all participants will undergo traditional cognitive stimulation therapy, embracing within each session paper-and-pencil and computerized activities during a face-to-face interaction with the therapist at the rehabilitation service. Activities will target memory, attention, and executive functions (24, 25); the level of difficulty will be tailored on the patients’ neuropsychological profile and progressively adjusted based on patients’ response to the treatment. Each session of cognitive training will last 40 min and will follow the brain stimulation session.

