## Discussion

3

The present study will investigate the feasibility and efficacy of an advanced, integrated, multifocal tDCS-EEG stimulation protocol in conjunction with cognitive treatment for the management of cognitive and affective symptoms observed in MCI and early-stage dementia. The project will contribute to a substantial shift in the framework of available non-pharmacological interventions for such clinical pictures, integrating different techniques and levels of analysis in a single, comprehensive protocol. This will be achieved by four key strategies: firstly, by adopting a new multifocal protocol that allows the simultaneous stimulation of fronto-temporal regions non-invasively (12, 42); secondly, by integrating the protocol with other non-pharmacological interventions to potentially enhance the mechanisms at play; thirdly, by identifying potential electrophysiological markers to brain stimulation (10); fourthly, by exploring the factors that may modulate the response to the intervention (7). The implementation of these strategies will enable the profiling of patients who are most likely to respond to brain stimulation as a rehabilitative tool (43). In such an integrated approach, the use of brain stimulation combined with conventional cognitive therapy will allow to strengthen the plasticity-driven mechanisms associated with the behavioral treatment. Moreover, the combination in the same protocol of EEG recording will allow monitoring the brain response associated with the treatment itself. The project may provide valuable insights into the intricate changes that occur in functional brain networks during pathological ageing (44–47) and potentially effective treatment procedures.

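### Individual responders to stimulation cannot be identified from one real and one sham block per patient, and the planned regression does not model the real-versus-sham effect

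*Protocol article*

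**What the plan says.** The responder aim appears in four places, with varying firmness.

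- Abstract, Method: "Analysis of electrophysiological data will contribute characterizing responders to treatment".
- Section 1, Background, on the rationale for combining EEG with stimulation: the combination "would allow identifying good and bad responders to stimulation", so that those likely to benefit most can be targeted.
- Section 1, Background, closing paragraph: the authors expect EEG to give findings useful to "distinguish good and bad responders to the treatment based on individual analysis".
- Section 3, Discussion: the strategies "will enable the profiling of patients who are most likely to respond to brain stimulation".

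The design is set out in sections 2.3 and 2.4. The 16 sessions "will be delivered in two blocks (8 real and 8 sham stimulation sessions"), so neither condition is repeated. On testing after the T1 baseline: "The same battery of tests will be repeated at the end of the first (T2) and of the second (T3) rehabilitation cycles". The battery is not repeated after the one-week washout. EEG is recorded around four sessions ("namely sessions 1, 8, 9 and 16; Figure 1) will be preceded and followed by 5-min resting state EEG recordings"), which makes eight recordings per patient, four in each block.

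Section 2.8 plans multiple regression of post-intervention MoCA, FAB and functional independence on gender, age, education, cognitive reserve and baseline EEG power. Sequence and carryover are examined only by an exploratory comparison of the two arms. The article gives no responder definition, no cut-off and no estimate of retest error.

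**The concern.** To call one patient a good or bad responder is to say that this patient's effect of real over sham differs from other patients' effects. That needs an estimate of the effect within the person and a measure of its error. Here each clinical test gives one post-real and one post-sham score per person. Within that person, real versus sham is also period 1 versus period 2, or the reverse. Nothing is replicated that would show how far the difference would move on repetition.

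If EEG features were then related to such individual differences, an apparent marker of response could reflect retest error or, if a period effect exists, allocation order. The Background gives the selection of patients for treatment as the purpose of such a marker, so a false one would have consequences. A period shift is plausible: cognitive therapy runs through both blocks and the same tests are given three times.

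**Working it through.** **The plan's own figure.** The article states no retest correlation, but its sample size implies one. Take the repeated-measures ANOVA interaction with k = 2 groups, m = 3 times, f = 0.25, ε = 0.75, α = 0.0125 and N = 48:

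- λ = f²·N·m·ε/(1 − ρ) = 0.0625 × 48 × 3 × 0.75/(1 − ρ); at ρ = 0.5 this is 13.5.
- df = (k − 1)(m − 1)ε = 1.5 and (N − k)(m − 1)ε = 69.
- Power = 0.816, and 48 is the smallest even N that reaches 0.80. With ρ = 0.3 the answer is 66, and with ρ = 0.7 it is 30.

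So 48 reproduces at ρ = 0.5.

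**The individual difference.** In outcome-SD units, let D be the score after real minus the score after sham:

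D = τ ± π + (e_real − e_sham)

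Here τ is the patient's true response. The period shift π has a plus sign for G1 (sham first) and a minus sign for G2 (real first). Each error has variance 1 − r, where r is retest reliability. Taking τ as independent of the errors and removing the average period shift:

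Var(D) = SD_τ² + 2(1 − r), and the share due to true response = SD_τ²/[SD_τ² + 2(1 − r)].

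The trial will observe Var(D) but not its two parts. Separating them would need a repeated real or sham condition.

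**Size under assumptions.** Neither r nor SD_τ is in the article; both are varied here.

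| r | 2(1 − r) | SD_τ 0.1 | SD_τ 0.2 | SD_τ 0.3 | SD_τ 0.5 |
|---|---|---|---|---|---|
| 0.7 | 0.6 | 2% | 6% | 13% | 29% |
| 0.8 | 0.4 | 2% | 9% | 18% | 38% |
| 0.9 | 0.2 | 5% | 17% | 31% | 56% |

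For example, at r = 0.8 and SD_τ = 0.3: 0.09/(0.09 + 0.4) = 18%. If ρ = 0.5 from the sample size is read as the retest correlation, 2(1 − ρ) = 1.0. The share is then 0.0625/1.0625 = 6% at SD_τ = 0.25, 0.25/1.25 = 20% at 0.5, and 50% only at 1.0.

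**What that means for a label.** If patients were split at the mean of D, agreement with truly above- or below-average response would be 0.5 + arcsin(√share)/π. That is 54% at r = 0.7, SD_τ = 0.1, and 77% at r = 0.9, SD_τ = 0.5, where 50% is chance. If every patient had the same true gain of 0.3 SD and there were no period effect, the proportion with D ≤ 0 would be Φ(−0.3/√[2(1 − r)]): 35%, 32% and 25% at r = 0.7, 0.8 and 0.9. These splits are illustrations; the article states no rule.

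**Sequence.** With an assumed shift π = 0.2 SD and no variation in τ, the proportion above the mean effect is Φ(±0.2/√[2(1 − r)]). That is 60% in G1 and 40% in G2 at r = 0.7, and 67% and 33% at r = 0.9. With π = 0 and no carryover, the two groups are equal.

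**The planned regression.** Its criterion is a level after intervention. The listed predictors include neither treatment nor sequence. A patient with favourable EEG who scores high after both real and sham would count in favour of EEG as a predictor, with no response to stimulation at all. It therefore asks who scores high, not who responds.

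**The case against.** The best defence is that the article plans no classification. It states no cut-off and no individual score, and the one analysis of this kind, in section 2.8, is a group-level regression on continuous outcomes. The closing Background paragraph states an expectation, not a promise. The Discussion's profiling aim is one that group-level modelling could serve. Details of an individual analysis may sit in a fuller document, and no primary or secondary comparison depends on them.

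Much of this stands. A reader might infer that the investigators will sort patients into two classes; the article does not say so. A reader might also infer that each patient supplies only two data points. That is wrong for EEG, which is recorded four times per block, and each test also has a T1 baseline. These data do not repeat the real-versus-sham contrast, however, so they do not repair the individual estimate.

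Two things survive the defence. The missing replicate is a feature of the design, so no analysis plan can supply it. And the group-level regression that is planned has the wrong criterion for a question about response.

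**Conclusion.** The point holds in this form: with one real and one sham block per patient, an individual real-minus-sham difference cannot separate true response from retest error and period, and section 2.8 contains no analysis of how the real-versus-sham effect varies with EEG. Neither statement depends on an assumed number.

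The size does. True response makes up about 2% to 56% of the variance of the individual difference for reliability 0.7 to 0.9 and response SD 0.1 to 0.5. It exceeds half in only one of the twelve combinations tabulated (0.9 with 0.5).

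A reader might go further and infer that responder findings will be mostly noise and allocation order. The documents do not support that as a general statement. The noise share rests on two quantities they do not give. The sequence part needs a non-zero period or carryover effect, and an average period shift can be removed at group level.

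The main treatment comparison is not affected. The change is still worth making, because responder identification is presented as one of the protocol's novel features.

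**What to change.** **Wording.** In the Abstract (Method), in both Background statements and in the Discussion, restate the aim as an exploratory group-level question: does the real-versus-sham effect vary with baseline EEG power?

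**Section 2.8.** Test this as a treatment-by-baseline-EEG interaction on the continuous outcome, with a period term, and label it exploratory. With complete data, regressing the real-minus-sham difference on baseline EEG power and a sequence indicator answers the same question.

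**Individuals.** Do not label patients as good or bad responders. If individual differences are shown, adjust them for period, display them against retest error and call them descriptive.

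**Cost.** No new data or visits are needed. The price is a less ambitious claim and low power. With 60 complete patients, one EEG feature, two-sided α = 0.05 and power 0.80, the smallest detectable correlation with D is about tanh[(1.96 + 0.84)/√57] = 0.35. Retest error dilutes the correlation by √share. At r = 0.8 and SD_τ = 0.3, the correlation of EEG with true response would have to be about 0.35/√0.18 = 0.8; in the most favourable cell of the table, 0.35/√0.56 = 0.5. A null interaction should therefore not be read as showing that EEG is irrelevant.

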## Method

2

### Study design

2.1

The study will adopt a double-blinded crossover randomized controlled design involving two clinical centers in Italy. The whole intervention will consist of two treatment phases (sham vs. real multifocal stimulation) and multiple assessment phases (T1, T2, T3). One-week washout will be interleaved between the two treatment phases (see Figure 1).

**Figure 1 fig1:**
[figure not shown]
Overview and schedule for the study protocol. Participants will be randomized in two groups receiving two cycles of sham/real brain stimulation (G1) or real/sham stimulation (G2) with 1-week washout combined with cognitive therapy. Each cycle will involve eight sessions (S1–S8, S9–S16) twice-weekly. Neuropsychological assessment will be performed before and after each intervention (T1–T3). ADL: Activities of Daily Living; IADL: Instrumental Activities of Daily Living. CGS: Geriatric Depression Scale; CRS: Cognitive Reserve Scale; MOCA: Montreal Cognitive Assessment; FAB: Frontal Assessment Battery; FCSRT: Free and Cued Selective Reminding Test.

### Participants

2.2

The recruitment centers for the study will be “Alma Mater Camaldoli Hospital” (Naples) and the Neuropsychological Testing Service of the Department of Psychology of University of Campania “Luigi Vanvitelli” (Caserta) in Italy. All participants consecutively admitted to the two centers will be screened for study participation. Data collection will be terminated when at least 60 participants will complete the whole intervention. Inclusion criteria are: (i) age between 55 and 85 years, and (ii) diagnosis of minor neurocognitive disorder, or major neurocognitive disorder with mild severity, according to Diagnostic and Statistical Manual of Mental Disorders [DSM-5; (20)] with a Clinical Dementia Rating Scale (CDR) of 0.05 or 1 (21), (iii) right handedness. The diagnosis will be made by expert neurologists and neuropsychologists. Exclusion criteria are: (i) brain events with an acute aetiology (stroke, traumatic brain injury, neoplastic ablation), (ii) psychiatric disorders (schizophrenia, psychosis, bipolar disorder) and assumption of psychotropic drugs, (iii) diagnosis of moderate or severe major neurocognitive disorders [DSM-5; (20)] with CDR scores equal or above 2 (21), (iv) any condition which might even hypothetically interfere with electrophysiological recording and neurostimulation (metallic implants in the brain, cochlear implant, pacemakers, epilepsy) (22, 23).

